### Interim analyses {21b}

No interim analyses are planned.

### Methods for additional analyses (e.g., subgroup analyses) {20b}

If a significant interaction is detected between demographic variables, youth depression, and/or parent distress, the study team will conduct subgroup analysis and examine each of the component effects using mixed model regression within subgroups for that moderator.

### Methods in analysis to handle protocol non-adherence and any statistical methods to handle missing data {20c}

The primary intention-to-treat (ITT) analyses will be based on all available data. Given the longitudinal design, we anticipate missing data will mostly occur in the outcome variables. For patient-reported outcomes, subjects may miss one or more of the 5 assessments. Repeated measures analysis based on mixed effects regression models can be performed on data with intermittent missing, that is, subjects will be included in the analysis as long as they have at least one observed outcome value.

The amount of missing data and pattern of missing data will be examined at each time point (T1–T5). Simple imputation using the “best” and “worst” scenarios for missing data will help identify the influence of missing data on the study results. If a substantial amount of missing data exists, in addition to our primary data analysis using all available data, we will conduct sensitivity analysis using multiple imputations with multivariate imputation using the chained equations (MICE) technique, assuming missing at random. Missing values are imputed based on the observed values for a given individual and the relations observed in the data from other participants, assuming the observed variables are included in the imputation model. Multiple imputation procedures, particularly MICE, are very flexible and can be used in a broad range of settings. Because multiple imputation involves creating multiple predictions for each missing value, the analyses of multiply imputed data take into account the uncertainty in the imputations and yield more accurate standard errors. The MICE approach is a flexible yet powerful technique to address missing data issues and has demonstrated excellent performance in practice [58–60].

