### Sample size {14}

We plan to enroll a total of 374 youth-parent dyads across all participating study sites. Three hundred sixty-eight participants will be included in the analyses. The six other participants are considered “training participants,” who will not be randomized and will receive treatment pathway 1 (all intervention components) for the purpose of providing an opportunity for each interventionist to practice intervention delivery with 1–2 families prior to the enrollment of actual study participants. Power analyses were conducted using FactorialPowerPlan SAS Macro for Aims 1 and 3, and PASS for Aim 2 to determine the appropriate number of participants for the study. The factorial design involves 3 completely crossed factors, and thus the same power calculation applies to each factor being tested, and to interaction effects also, since this is a 2^3^ factorial. Based in part on prior investigations by the study team,^1^ assumptions include: 5 assessment points (baseline, 6 weeks, 3 months, 6 months, and 12 months), within-subject correlations over time of *ρ* = 0.6, two-tailed alpha = 0.05, and 10% 12-month attrition were used for all power analyses. In the prior single-site R01 trial, the study team observed 6–12-month HBI treatment effects ranging between 0.26 and 0.32 and PedsQL treatment effects ranging between 0.19 and 0.29. The proposed sample size of 368 (184 per factor present vs. absent comparison) provides power > 0.80 to detect a small effect size of Cohen’s *d* = 0.15 under these assumptions. In terms of the cell size of the factorial design, we will allocate 46 participants to each of the 8 groups and retain an average of 42 participants within each. In terms of power to detect mediation for Aim 2, with “a” the standardized coefficient between the component group and the mediators = 0.34, “b” the standardized coefficient between the mediators and PedsQL/HBI symptom outcomes = 0.34, and with 368 patients, 10% attrition and alpha set at 5%, the power = 0.80 to detect minimal indirect/mediated effect 0.12 [54]. With a total sample size of 368, the component group by moderator interaction effect size was estimated using ANCOVA with baseline HBI or PedsQL as the covariate. With the probability of a 2-tailed type I error set at 5%, the study will have ≥ 0.80 power to detect a component group by moderator interaction ES = 0.25 for 12-month HBI or PedsQL.

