where *Y*_*ij*_ is the outcome for subject *i* at time *j*, *b*_0*i*_ is the subject-specific random intercept to account for within-subject correlation due to repeated measures, and *CHIP*_*i*_ × *Time*_*j*_ is the intervention-by-time interaction term. *CHIP*_*i*_ takes value 1–8 representing each of the 8 combinations of cf-CBT, PS, and CM. *X*_*i*_ is a vector of covariates including baseline injury severity, birth sex, and referring site. We will model *Time*_*j*_ as a discrete variable given a limited number of assessments, the coefficients of the intervention-by-time interaction β_3_ estimate the mean differences between treatment arms in changes (“difference-in-differences”) at later time points relative to baseline. The significance of these coefficients will be assessed using confidence intervals, and *p*-values from *F*-tests based on ANOVA and the Kenward-Roger method [55]. For Aim 1a, we will examine component effects on youth headache, depressive symptoms (PHQ-9) and sleep (ASWS), and parental distress regarding their child’s illness (PIP) using the same methods.

Using our importance criteria, for intervention optimization, we will consider any components or interactions demonstrating an effect size of 0.20 on either the HBI or PedsQL to be worth retaining in the optimized intervention. We will make our initial decision at 6 months, but will also examine 12-month HBI and PedsQL outcomes. We are balancing effectiveness and efficiency in our optimized intervention by not including components that demonstrate a small effect (Cohen’s *d* = 0.20) at 6 or 12 months on the HBI or PedsQL.

#### Aim 2

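### The planned missing-data sensitivity analyses do not usefully probe departures from missing at random near the 0.20 retention threshold

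*Protocol article*

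**What the plan says.** Section {20c} of the protocol article describes three layers.

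- **Primary:** intention-to-treat mixed models on all available data, where "subjects will be included in the analysis as long as they have at least one observed outcome value".
- **First check:** "Simple imputation using the “best” and “worst” scenarios for missing data will help identify the influence of missing data on the study results". The section does not say which values are imputed, or whether the two levels of a component receive the same end of the scale or opposite ends.
- **Second check:** "If a substantial amount of missing data exists", a "sensitivity analysis using multiple imputations with multivariate imputation using the chained equations (MICE) technique, assuming missing at random". No amount is attached to the condition.

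These analyses serve a rule under Aim 1, which considers "any components or interactions demonstrating an effect size of 0.20 on either the HBI or PedsQL to be worth retaining". On timing, Aim 1 says: "We will make our initial decision at 6 months, but will also examine 12-month HBI and PedsQL outcomes". For expected loss, Sample size {14} states that "10% 12-month attrition were used for all power analyses".

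**The concern.** A sensitivity analysis should vary the assumption that the primary analysis rests on. A likelihood-based mixed model on all available data is valid under missing at random (MAR). The article does not say so at that point, but it is a property of the method. MICE under MAR leaves that assumption where it was. The only step that moves it is single imputation at extremes. That step treats imputed values as observed, although the same section credits multiple imputation with carrying imputation uncertainty into the standard errors.

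Outcome-related dropout that differs by component is plausible. Families are told their group, outcomes are self-reported, and contact ranges from 0 to 19 sessions. From Table 1, each component averages (19 + 13 + 13 + 7)/4 = 13 sessions when present and (13 + 7 + 7 + 0)/4 = 6.75 when absent.

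At stake is the choice of components for the optimised package. The full package earlier showed effects of 0.26 to 0.32 on HBI and 0.19 to 0.29 on PedsQL (Sample size {14}), so single-component effects may well lie near 0.20. There a small bias from dropout can decide retention.

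**Working it through.** **Inputs from the article.** HBI: 20 items on a 4-point scale, so with unit steps the span is 20 × 3 = 60 points (Primary outcome measures). Attrition: 10% at 12 months; 46 allocated and 42 retained per cell (Sample size {14}). Threshold: 0.20 (Aim 1).

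**Assumptions.** The article gives no SD for HBI. I take 10 to 15 points and widen to 8 to 20. The 10% is a 12-month figure and the first decision is at 6 months, so I also use 5%.

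**Step 1. Reproduce the retention figure.** 46 × (1 − 0.10) = 41.4, against a stated average of 42. The stated figures imply a loss of 4/46 = 8.7%. The two agree closely enough to use both.

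**Step 2. Opposite scale ends.** Let a fraction m be missing in each level of a component. Set missing values to one end of the scale in one level and to the other end in the other level. The standardised contrast d becomes

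(1 − m)d ± m × 60/SD.

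| m | SD 10 | SD 12 | SD 15 |
|---|---|---|---|
| 5% | 0.30 (1.5 × threshold) | 0.25 (1.25 ×) | 0.20 (1.0 ×) |
| 8.7% | 0.52 (2.6 ×) | 0.43 (2.2 ×) | 0.35 (1.7 ×) |
| 10% | 0.60 (3.0 ×) | 0.50 (2.5 ×) | 0.40 (2.0 ×) |

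The extremes over SD 8 to 20 and 5% to 10% missing are 0.10 × 60/8 = 0.75 (3.75 ×) and 0.05 × 60/20 = 0.15 (0.75 ×).

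The imputed extremes also inflate the SD. Within a level the variance becomes (1 − m)SD² + m(1 − m)(end − mean)². Dividing by the resulting pooled SD, with m = 10%, SD 10 to 15 and an assumed mean of 15 to 25, gives a shift of 0.34 to 0.46 (1.7 to 2.3 ×).

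For d = 0.20 and m = 10%, the bounds are 0.18 ± 0.60 = −0.42 to 0.78 (SD 10) and 0.18 ± 0.40 = −0.22 to 0.58 (SD 15).

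**Step 3. Which estimates would these bounds settle?** With m = 10% and SD 15, both scenarios favour retention only if 0.9d − 0.40 ≥ 0.20, that is d ≥ 0.67. Both favour dropping only if 0.9d + 0.40 < 0.20, that is d < −0.22. Every earlier full-package effect (0.19 to 0.32) lies between these limits.

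**Step 4. Same scale end in both levels.** With equal attrition the imputed parts cancel and the contrast becomes (1 − m)d: 0.9 × 0.20 = 0.18. An estimate at the threshold falls below it mechanically, whatever the dropouts' true outcomes. With unequal attrition, say 8% against 12%, an assumed mean of 20 and SD 12, the shift is 0.04 × 40/12 = 0.13 at the high end or 0.04 × 20/12 = 0.07 at the low end. It reflects the distance to the scale end, not a credible departure.

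**Step 5. A modest departure.** Shifting the imputed values in one level by δ SD moves the contrast by m × δ. At 10% missing, δ = 0.5 gives 0.05, so a MAR estimate between 0.20 and 0.25 could cross the threshold. Moving 0.20 to zero needs δ = 2.

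PedsQL follows the same formulas, but the article gives neither its score range nor its SD, so I have not put a figure on it.

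**The case against.** Several points against this are fair.

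- **The article is condensed and the SAP is not shown.** The definitions of best, worst and substantial, the imputation model and any graded analysis may stand there. A reader might infer that no graded analysis will be done, but the article does not establish that. What remains is what section {20c} does state: the role given to MICE under MAR, and the best/worst step as the way to see the influence of missing data.
- **A reader might say that the planned analyses fail to test MAR.** No analysis of observed data can test it, delta adjustment included. Best/worst imputation is itself a departure from MAR, only a crude one.
- **MICE need not reproduce the mixed model.** Table 3 lists PHQ-9, GAD-7, PIP and parent-report PedsQL at every visit. As auxiliary variables they could make MAR more plausible and change the estimate. That is useful, but it still does not examine departures from MAR.
- **A reader might infer that the bounds are always two to three times the threshold, or span both decisions whatever the data show.** Neither holds. The multiple depends on an SD, a missing fraction and a reading of the scenarios that the article does not give. With 10% missing and SD 15, an estimate of 0.70 keeps a lower bound of 0.63 − 0.40 = 0.23, and one of −0.30 has an upper bound of −0.27 + 0.40 = 0.13. At 2% missing the shift is only 0.08 to 0.12 for SD 15 to 10.
- **Differential dropout is not shown.** Group 8 is only one of four cells in each absent level, participants who stop sessions stay in the analysis, and incentives are tied to survey completion. Dropout of this kind is plausible, not predicted.
- **The effect of a modest departure is small.** At 0.05 SD it matters only for estimates already close to 0.20, which limits the weight of the point.

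**Conclusion.** The concern holds in a limited form. As described, MICE under MAR shares the primary model's assumption, runs only on an unquantified trigger, and cannot show what departures from MAR would do. The one other check ignores imputation uncertainty and has the wrong resolution. The opposite-ends version moves the HBI contrast by 0.40 to 0.60 SD at 10% missing and 0.35 to 0.52 SD at 42 of 46 retained, for an assumed SD of 10 to 15. Over 5% to 10% missing and SD 8 to 20, that is 0.75 to 3.75 times the threshold. The same-end version with equal attrition only shrinks 0.20 to 0.18. For estimates near 0.20, neither shows whether a retention decision depends on modest outcome-related dropout. The primary analysis is not wrong. This is a change that should be made, not an obstacle to the trial.

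**What to change.** In section {20c}, replace or supplement best/worst imputation with delta-adjusted multiple imputation:

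- Include the three component indicators and the baseline outcome in the imputation model.
- Shift the imputed values separately by component level, for example from 0 to 0.5 SD in steps of 0.1 SD, and further if no decision changes.
- Apply it to HBI and PedsQL at 6 and 12 months, and report the smallest shift that changes a retention decision.
- Run it whether or not missingness is judged substantial.
- Describe MICE under MAR as a supporting analysis, not as a check on MAR. If best/worst imputation is kept, define the values and their direction by component level.

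The cost is a little more analysis work, using the imputation code already planned, and a revised paragraph. It needs no new data and can be settled before follow-up ends in March 2028.

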### Plans to give access to the full protocol, participant-level data, and statistical code {31c}

The PIs and co-investigators are willing to share data and materials with other eligible investigators through academically established means as soon as they have published their research results. We accept full responsibility to protect the rights of participants and the confidentiality of the data collected in this study. In these data-sharing efforts and with any others that may arise in the future, we will enter into data-sharing agreements prior to exchanging study data. These agreements will include the following requirements (1) researchers outside of the study team will submit a research plan proposal for PI approval prior to receipt of any data, (2) data recipients agree not to attempt to identify individuals who are subjects of the data, (3) data recipients will participate in regular check-in meetings with the study PIs during the analysis process, and (4) at least one of the study PIs ([name] or [name]) will review all manuscripts prior to submission to verify that data are accurately described and represented.

### Oversight and monitoring

#### Composition of the coordinating center and trial steering committee {5d}

This study does not have a coordinating center or a trial steering committee. Seattle Children’s Research Institute is the main study site with UTSW as a participating site. The study team is made up of four investigators who provide weekly oversight over study procedures, two research coordinators responsible for recruitment, informed consent, and data management, as well as three therapists who deliver the intervention components. We also have two individuals supporting data analysis, a statistician and a multiphase optimization strategy (MOST) expert, who will be particularly engaged in the later years of the trial.

#### Composition of the data monitoring committee, its role and reporting structure {21a}

The study has an external, independent DSMB. The board consists of a pediatric neuropsychologist who specializes in the assessment and treatment of youth with concussion (who will also serve as the Board Chair), a quantitative biostatistician, and an adolescent health bioethicist. The study team will meet with the DSMB approximately every 6 months throughout the study to review recruitment and follow-up, protocol deviations, and adverse events. The board will conduct reviews of study progression and data integrity, including assessments of attainment of study recruitment milestones, adequacy of follow-up, and potential sources of bias and threats to internal validity The board reports directly to the study sponsor, NICHD.

#### Adverse event reporting and harms {22}

The adolescent study population is known to experience a number of adverse events (AE) after concussion injury that are not expected to be study-related. For instance, based on prior study team investigation, it is anticipated that a subgroup of adolescents recruited into the investigation may have pre-concussion mental health symptoms that may contribute to suicidal ideation and even suicide attempts while enrolled in the investigation. Adolescent suicide attempts are defined as a serious adverse event (SAE) for the study as are any emergency department visits/hospitalizations that are associated with suicidal ideation or intent.

The study team may become aware of AEs/SAEs through routine interactions with study subjects, such as while scheduling, during baseline or follow-up surveys, or during intervention sessions Study team members will ensure that the DSMB members are made aware of any relevant problems, or SAEs.

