## Interventions

### Explanation for the choice of comparators {6b}

The study includes 8 different treatment arms, as specified in Table 1 below.

**Table 1 Tab1:** Intervention treatment groups

Treatment group	Percentage in this group	Sessions
1	12.5%	Treatment group 1 receives cognitive behavioral skills for concussion, parenting skills training, and care management (19 sessions total)
2	12.5%	Treatment group 2 receives cognitive behavioral skills for concussion and parenting skills training (13 sessions total)
3	12.5%	Treatment group 3 receives cognitive behavioral skills for concussion and care Management (13 sessions total)
4	12.5%	Treatment group 4 receives cognitive behavioral skills for concussion (7 sessions total)
5	12.5%	Treatment group 5 receives parenting skills training and care management (13 sessions total)
6	12.5%	Treatment group 6 receives parenting skills training (7 sessions total)
7	12.5%	Treatment group 7 receives care management (7 sessions total)
8	12.5%	Treatment group 8 receives surveys only (0 sessions)

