### Intervention description {11a}

#### Introductory session

All participants assigned to treatment groups 1–7 will be invited to participate in an introductory session, which includes psychoeducation and collaborative development of goals for treatment. For treatment groups 1, 2, and 3, both youth and parents will participate in the introduction session. For treatment group 4, only the youth will participate in the introduction session. For treatment group 6, only the parent will participate in the introduction session. For treatment groups 5 and 7, the parent will participate with the youth optional.

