#### Component 1: concussion-focused cognitive behavioral therapy (cf-CBT)

The cf-CBT component targets post-concussive symptoms including mood, pain, and sleep by teaching adolescents established evidence-based emotion regulation, relaxation, and behavioral and cognitive strategies to manage their symptoms. Homework/practice assignments are given to help adolescents apply in-session concepts to the management of their symptoms. Youth randomized to receive this component will participate in six 30-min sessions of cf-CBT.

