#### Component 3: care management (CM)

In the CM component, parents are provided support regarding advocating for their child’s needs across different contexts in the healthcare system, school, and athletic departments (including guidance regarding medication referrals), using applied problem-solving together with the skills coach to address emergent needs. Adolescents can also be involved in CM, if developmentally appropriate based on their age, independence, and interest. Of note, while the CM component engages youth and parents, treatment effects are hypothesized to result from facilitating access to supportive services including medication referrals at the organizational level. Families randomized to receive this component will participate in six 30-min sessions of CM.

Treatment groups 1–7 will receive 7–19 sessions based on their group assignment (see Table 1) and these will be delivered over 12 weeks. Each half-hour intervention session will only address one of the three unique components, and the cadence of delivery of each component (Table 2) will allow all sessions to be completed during the 12-week intervention time frame, with a maximum of 10 h of intervention for families receiving all components. Components will be interspersed to allow time to practice and use skills in between sessions, and to mimic the manner in which treatment would be delivered clinically.

**Table 2 Tab2:** Description of intervention components and dosage

Intervention component	Primary recipient	Core intervention elements	Intervention dosage
Concussion-focused cognitive behavioral therapy (cf-CBT)	Youth	Emotion regulation, relaxation training, behavioral and cognitive strategies to manage symptoms	6 half-hour sessions, delivered within the first 3 months
Parenting skills training (PST)	Parent	Parenting behavior, stress management, and positive family communication	6 half-hour sessions, delivered within the first 3 months
Care management (CM)	Parent and youth	Care coordination coaching across medical, educational, and sports settings; psychoeducation and working with medical providers on medication referrals when needed	6 half-hour sessions, delivered within the first 3 months

#### Usual care for treatment group 8

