##### Health service and medication utilization

Parent reports will be used to assess adolescents’ pre- and post-sports injury health service utilization. Parents will report the specific number of visits to the emergency department, primary care provider, and subspecialty providers over the prior 6 months. Parents will also report on the types of medication used by adolescents (Table 3
).

**Table 3 Tab3:** Study assessments, use, and administration

Construct	Measure	How used	Baseline	6 weeks	3 months	6 months	12 months
Post-concussive symptoms	HBI	Primary outcome	A	A	A	A	A
Health-related quality of life	PedsQL	Primary outcome	A, P	A, P	A, P	A, P	A, P
Depressive symptoms	PHQ-9	Proximal outcome; moderator	A	A	A	A	A,
Anxiety symptoms	GAD-7	Proximal outcome	A	A	A	A	A
Sleep quality	ASWS-SF	Proximal outcome	A, DD	A	A, DD	A, DD	A, DD
Headache pain	NRS-11	Proximal outcome	DD		DD	DD	DD
Treatment acceptability and satisfaction	TEI-SF	Proximal outcome			A, PS		
Parent distress regarding their child’s illness	PIP	Proximal outcome; moderator	PS	PS	PS	PS	PS
Parent self-efficacy regarding engaging with health care	P-PAM	Proximal outcome, mediator	PS	PS	PS	PS	PS
Adolescent self-efficacy	GSE	Mediator	A	A	A	A	A
Parental protectiveness	ARCS	Mediator	PS	PS	PS	PS	PS
Youth prior psychiatric and concussion history		Descriptive	P				
Demographic characteristics		Descriptive	A, PS				
Health care utilization		Descriptive	P			P	P

*A* adolescent, *P* parent report of adolescent, *PS* parent self-report, *DD* daily diary

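### Adverse events are picked up passively, and one named source (intervention sessions) ranges from 0 to 19 by assignment, so counts by group or component may reflect contact as well as harm

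*Protocol article*

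**What the plan says.** The section on adverse event reporting and harms {22} states how events reach the team: "The study team may become aware of AEs/SAEs through routine interactions with study subjects". Scheduling calls, surveys at baseline and follow-up, and treatment sessions are the examples given. The same section expects some suicidality in this population. It classes as serious any adolescent suicide attempt and any emergency visit or hospital stay linked to suicidality.

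The amount of session contact depends on assignment. The care management section says that "Treatment groups 1–7 will receive 7–19 sessions based on their group assignment", delivered over 12 weeks. In Table 1, group 8 has surveys and no sessions. The introductory session is also confined to the treated groups: "All participants assigned to treatment groups 1–7 will be invited to participate in an introductory session".

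Several sources are the same in every group. Surveys are triggered automatically at 6 weeks and 3, 6 and 12 months. Table 3 has each adolescent complete the PHQ-9 and GAD-7 at every survey, and daily diaries at baseline and 3, 6 and 12 months. Health care use is reported by parents at baseline, 6 and 12 months and is labelled descriptive: "Parents will report the specific number of visits to the emergency department, primary care provider, and subspecialty providers over the prior 6 months".

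Under {17a}, only the statistician and the fidelity coders are blinded. The therapists and coordinators who would notice an event know the assignment.

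**The concern.** If an event enters the record because someone happens to hear of it, the chance of recording depends on how often staff and family meet. Here randomization sets part of that contact. With the same true risk in every group, more events may come to light where more sessions are delivered. Because every component adds sessions, this affects all three component contrasts as well as the comparison with group 8.

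Two errors are possible. A component could appear to carry more events only because it brings more contact, or a real reduction in events could be hidden by better detection. Separately, a serious event in a surveys-only family might never reach the DSMB, which is charged with reviewing adverse events and possible sources of bias.

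**Working it through.** **Session counts.** The inputs are one introductory session for groups 1–7 and six sessions per component (component descriptions and Table 2).

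Sessions = 1 + 6 × number of components for groups 1–7, and 0 for group 8.

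- Three components: 1 + 18 = 19 (group 1)
- Two components: 1 + 12 = 13 (groups 2, 3, 5)
- One component: 1 + 6 = 7 (groups 4, 6, 7)
- None: 0 (group 8)

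This reproduces Table 1 exactly.

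**Imbalance in each component contrast.** Each contrast sets four cells against four:

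- Present: (19 + 13 + 13 + 7)/4 = 13.0
- Absent: (13 + 7 + 7 + 0)/4 = 6.75

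By symmetry the result is the same for all three components.

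**What the common sources record, as described.**

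| Source | When | Attempt recorded? | Reason for emergency visit or hospital stay? |
|---|---|---|---|
| PHQ-9, GAD-7 | every survey | not described; symptom severity | no |
| Daily diary | baseline, 3, 6, 12 months | not described; headache, mood, energy | no |
| Parent-reported visits | baseline, 6, 12 months | no | not described; visit counts |

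The visit item looks back 6 months, so the answers at 6 and 12 months together cover the whole follow-up, including the 12 treatment weeks. The gap is in content: a suicide-related emergency visit cannot be told from another visit, hospital stays are not named, and an attempt without a visit leaves no trace.

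**Illustration of size.** The document gives no detection probabilities, so s and q below are assumptions. Let s be the chance that an event becomes known through surveys and scheduling (taken as equal in all groups), q the chance per session, and m the number of sessions. Then

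P(known) = 1 − (1 − s)(1 − q)^m.

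For s = 0.3 and q = 0.05, group 1 gives 1 − 0.7 × 0.95^19 = 0.74 and group 8 gives 0.30. Component values are averages over the four cells.

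| s | q | Group 1 | Group 8 | Ratio | Present | Absent | Ratio |
|---|---|---|---|---|---|---|---|
| 0.3 | 0.05 | 0.74 | 0.30 | 2.45 | 0.63 | 0.49 | 1.29 |
| 0.5 | 0.05 | 0.81 | 0.50 | 1.62 | 0.74 | 0.64 | 1.16 |
| 0.7 | 0.02 | 0.80 | 0.70 | 1.14 | 0.77 | 0.74 | 1.04 |
| 0.9 | 0.02 | 0.93 | 0.90 | 1.04 | 0.92 | 0.91 | 1.01 |

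Across s from 0.3 to 0.9 and q from 0.02 to 0.10, the group 1 to group 8 ratio runs from 1.04 to 3.02. It is 1.00 when s = 1.

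These figures give every event the full m sessions in which to be noticed, so they are a ceiling for events in the treatment period. An event after week 12 has no scheduled session ahead of it. If events were spread evenly over a year, 12/52 = 0.23 would fall in the treatment period. The first row then becomes at most 0.30 + 0.23 × (0.74 − 0.30) = 0.40 against 0.30, a ratio of about 1.3. The third row becomes 0.70 + 0.23 × (0.80 − 0.70) = 0.72 against 0.70, about 1.03.

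**The case against.** The strongest case against runs as follows.

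- **Much of the contact is common to all groups.** This stands. Group 8 is not without ascertainment. A reader might infer from 4 follow-up surveys against 4 + 19 = 23 contacts that reporting chances differ about six-fold. The documents do not support that. The diaries at 3, 6 and 12 months are also common: counting each diary week once gives 7 against 26 (3.7), and counting each of the 21 diary days gives 25 against 44 (1.8). No such ratio measures reporting bias.
- **The treatment period is covered by the visit counts.** This stands. A reader might infer from the missing 6-week and 3-month entries that emergency visits during treatment go unasked, but the 6-month recall covers them in every group. Reasons for visits remain uncovered.
- **The imbalance lasts 12 weeks of a 12-month follow-up.** This stands and limits the size.
- **No comparison of harms between groups is stated.** This also stands. The DSMB reviews adverse events, but the article does not say by group. The point therefore concerns any such count that is made, and the events that never become known.
- **A condensed article may leave out the adverse event form.** This stands in part. The list of sources is illustrative, and the surveys might contain a suitable item. But the article does state a method of detection, and that method depends on assignment. The point rests on what is stated.

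**Conclusion.** The point holds in a limited form and is worth acting on. As written, detection is passive, and one named source differs by assignment for 12 weeks: 0 to 19 sessions, or 13.0 against 6.75 on average in each component contrast. The common measures are not described as capturing the events that the protocol defines as serious. Under equal true risk, the expected direction is more known events where more sessions are delivered, with serious events in group 8 possibly unknown.

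It would go too far to say that harms will look more frequent with more treatment. The size rests on detection probabilities that the document does not give. It could be negligible if the common sources catch nearly everything, and a true benefit of treatment could offset it. The illustration also assumes equal detection through common sources in all groups. If scheduling contact rises with the number of sessions, that assumption understates the gap.

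**What to change.** Add the same short adverse event items (suicide attempt; emergency visit or hospitalization, with reason) to the existing 6-week and 3-, 6- and 12-month REDCap surveys in all eight groups. Add one field recording how each event became known. Use survey-detected events for any figure by group or component that is given to the DSMB or published, and list session-detected events separately so that none is lost. The comparable figure then rests on four post-baseline enquiries that are identical in every group.

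The cost is a few survey items, one source field, an IRB modification and a small burden on respondents. Allocation, sessions and the efficacy analysis do not change. Recruitment is expected to run to about January 2027, so the change can still reach later families. Surveys completed before it would lack the items, and reports should give the date from which the common figure applies.
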